### Recruitment {15}

Breast cancer patients who have been treated at the GKH Breast Cancer Center and who have given their consent to be contacted for clinical studies will be briefly screened for eligibility, contacted by phone call, and invited to participate in this study. A clinical interview is scheduled with interested and eligible patients. After obtaining written informed consent and after the patient’s enrollment in this study, sociodemographic and clinical data (age, body mass index, tumor stage, hormonal status, concomitant medications, sports activities) are surveyed, and questionnaires will be given to participants.

### Assignment of interventions: allocation

#### Sequence generation {16a}

The randomization sequence has been created [34] using the website www.jerrydallal.com/random/random_block_size_r.htm with a 1:1 allocation, using block sizes of four to six. The randomization plan for subjects no. 1–40 was generated on 12 May 2020 (Seed No. 15277) and for subjects no. 41–60 on 2 March 2021 (Seed No. 15434).

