#### Concealment mechanism {16b}

In the temporal order of the study inclusion, allocation will be made according to the randomization plan to either the tango or the waiting group. Participants, physicians, and therapists are blinded to the randomization and allocation processes and will have no influence on the assignment of participants to each of both groups.

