#### Implementation {16c}

In a clinical interview, a study physician collects patient clinical and demographic data and provides information about the study. All patients who give their written consent to participate in the study will be enrolled in this study. Unique identifiers were generated using an ID-generator software [35]. A study investigator will register the participants, using the randomization plan to allocate to either the tango or waiting group. According to the availability to participate in a tango course, the participants are asked to complete and return the questionnaires at specified dates. The flow diagram of the study design is depicted in Fig. 1.

All patient data is handled in accordance with the General Data Protection Regulation (GDPR). All data from the participants will be maintained confidentially before, during, and after the trial and is stored securely at the study site, with limited access.

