
## Trial status

The current protocol version is 2.0, dated from 23 March 2020. The trial is ongoing and currently enrolling. The first participant was enrolled on 10 June 2020, and recruitment is expected to be finalized in the second quarter of 2022 with the follow-up completed by the end of March 2024.

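### Generator, seeds and block sizes are published while enrolment is open, so concealment is not assured for numbers not yet allocated

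*Protocol article*

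**What the plan says.** Section {16a} (Sequence generation) of the protocol article describes a list made "using the website www.jerrydallal.com/random/random_block_size_r.htm with a 1:1 allocation, using block sizes of four to six". It then gives the details of both parts: "The randomization plan for subjects no. 1–40 was generated on 12 May 2020 (Seed No. 15277" and, for the remainder, "for subjects no. 41–60 on 2 March 2021 (Seed No. 15434".

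Section {16b} (Concealment mechanism) states that numbers are used in the order in which participants are included. It claims that "Participants, physicians, and therapists are blinded to the randomization and allocation processes" and that these groups cannot influence assignment.

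Section {16c} (Implementation) says who applies the list: "A study investigator will register the participants, using the randomization plan to allocate to either the tango or waiting group".

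The Trial status section says: "The trial is ongoing and currently enrolling". It expects recruitment to end in the second quarter of 2022.

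**The concern.** A seed is recorded so that the same list can be produced again. That is useful for audit after the last allocation. Before then, it gives the next assignment to anyone who has the generator, the settings and the current position in the list. Here the position is easy to know, because the list is used in order of inclusion.

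What is at stake is selection before allocation. Under section {15} (Recruitment), candidates are screened, telephoned and invited to an interview before they are enrolled. If the next arm can be foreseen, whom to approach and when can depend on it, even unintentionally. The primary outcome is self-reported fatigue, and participants know whether they are receiving tango, so traits such as motivation or expectation could plausibly affect the result. This is separate from the lack of treatment blinding, which the design cannot avoid. Concealment of the upcoming assignment can be protected in an open-label trial.

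**Working it through.** The plan gives no figure to reproduce on this point. The check sets the sections side by side and then bounds the possible size.

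**1. What would be needed to regenerate the list, and what is printed**

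| Item | Printed? | Where |
|---|---|---|
| Generator | Yes, by web address | {16a} |
| Ratio | Yes, 1:1 | {16a} |
| Block sizes | Yes, as a range | {16a} |
| List lengths | Yes, 1–40 and 41–60 | {16a} |
| Seeds | Yes, 15277 and 15434 | {16a} |
| Order of use | Yes, by inclusion | {16b} |
| Exact block-size entry and order of arm labels | No | – |

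The plan words the block sizes as "using block sizes of four to six". A block of 5 cannot be balanced 1:1, so sizes 4 and 6 are the natural reading. For the settings that are not printed, a few candidate lists could be compared with allocations already made. Team members can know these: section {17a} has the research team request questionnaires according to allocation, and section {5d} has the team meet regularly with the study physicians and the tango teacher.

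The website was not run. Reproduction rests on the assumption that the generator returns the same list for the same seed and settings.

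**2. Other safeguards.** Sections {16a} to {16c} describe no sealed envelopes, central service or independent holder of the list that would still protect it after disclosure.

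**3. Predictability without the seed, for comparison.** A simulation of 100,000 lists of 20 participants used random balanced blocks of 4 or 6, assumed equally likely. The observer knows all past allocations and guesses the arm that is behind. The guess was right 68.5% of the time, against 50% by chance. If the seed and settings reproduce the list, the figure is 100%.

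**4. Number exposed.** Only participants allocated after the details became known are affected. The article does not say how many numbers were unallocated then. Assuming list 1–40 is used up, the count lies between 0 and 60 − 40 = 20, which is at most 20/60 = 33% of the sample.

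**5. Possible bias.** Let k be the number exposed. Suppose that steering creates a prognostic difference of 0.5 SD between the arms among those k, and none among the rest. The 0.5 SD is an assumption with no source in the article. With the exposed participants split evenly between arms, the overall bias is (k/60) × 0.5 SD. The planned effect of d = 0.8 comes from section {14}.

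| k | Bias | Share of d = 0.8 |
|---|---|---|
| 0 | 0 | 0% |
| 5 | 5/60 × 0.5 = 0.04 SD | 5% |
| 10 | 10/60 × 0.5 = 0.08 SD | 10% |
| 20 | 20/60 × 0.5 = 0.17 SD | 21% |

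The bias is proportional to the assumed difference, so halving 0.5 SD halves every entry.

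**The case against.** Several counter-arguments carry weight.

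- **Reproduction is not shown.** The exact block-size entry and the order of the arm labels are not printed, and the generator was not run. An outside reader with no knowledge of past allocations could not confirm a regenerated list. This stands. It limits the point to people who know past allocations, and to a probable rather than a demonstrated reconstruction.
- **The exposure may be small.** Neither the article's publication date nor the number already allocated is given. This stands, and it is why the size is given as a range that starts at zero.
- **Adjustment is planned.** Sections {20a} and {20b} plan adjusted regression and consider baseline outcome values, age, body mass index, tumour stage, endocrine treatment and sport activity. This could reduce bias from steering on those factors. It would not remove bias from unmeasured ones such as motivation.
- **Someone must hold the list.** That an investigator allocates from the plan is not in itself a breach, and the article does not say that this person also invites candidates. This stands. The article does not confirm a separation from recruitment either, but the point does not depend on a conflict of roles.
- **Random block sizes are a usual safeguard.** This is true. The 68.5% reflects a general limit of blocked lists and is not the reason for the finding. The reason is that the seeds are published.

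A reader might infer that the remaining sequence is already compromised, or that the results are biased. The documents support neither. They do not show that anyone regenerated the list or acted on it.

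**Conclusion.** The point holds as a weakness in protection. The article prints nearly everything needed to rebuild the list while enrolment is open, and it describes no other barrier. The concealment claimed in section {16b} is therefore not assured for numbers not yet allocated.

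The conclusion rests on three assumptions: the generator is deterministic for a given seed, the unprinted settings can be resolved against past allocations, and some numbers were still unallocated when the details became known. On the further assumption that list 1–40 is used up, 0 to 20 of 60 participants are exposed. The illustrative bias then runs from nil to 0.17 SD, and the top of that range needs both full exposure and the assumed 0.5 SD difference. It would be wrong to quote 0.17 SD alone as the expected effect.

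**What to change.** For every number not yet allocated:

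1. Replace the published list with a new one that uses an undisclosed seed and undisclosed, varying block sizes.
2. Have it held by existing staff who take no part in screening or inviting participants.
3. Release each allocation only after the participant has been irrevocably registered and the baseline CFS-D has been returned.
4. Publish the new seed and block sizes only after the last allocation.
5. Report how many participants were allocated after the details in section {16a} became public. If enrolment has already closed, this is the only step that remains.

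A comparison of results before and after disclosure is not recommended. With 60 participants, and perhaps only a few after disclosure, it would have almost no power, and a null result could reassure falsely.

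The cost is a short amendment and a small change in who holds the list. No extra staff or participants are needed.

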#### Concealment mechanism {16b}

In the temporal order of the study inclusion, allocation will be made according to the randomization plan to either the tango or the waiting group. Participants, physicians, and therapists are blinded to the randomization and allocation processes and will have no influence on the assignment of participants to each of both groups.

#### Implementation {16c}

In a clinical interview, a study physician collects patient clinical and demographic data and provides information about the study. All patients who give their written consent to participate in the study will be enrolled in this study. Unique identifiers were generated using an ID-generator software [35]. A study investigator will register the participants, using the randomization plan to allocate to either the tango or waiting group. According to the availability to participate in a tango course, the participants are asked to complete and return the questionnaires at specified dates. The flow diagram of the study design is depicted in Fig. 1.

All patient data is handled in accordance with the General Data Protection Regulation (GDPR). All data from the participants will be maintained confidentially before, during, and after the trial and is stored securely at the study site, with limited access.

### Assignment of interventions: blinding

#### Who will be blinded {17a}

All participants, physicians, and therapists are blinded to the randomization and allocation process. Due to the nature of the study design, participants are not blinded to the tango treatment itself; however, as the waiting-list control group will as well receive the same tango lessons later on, they will not know whether they are in the waiting list or not. According to their allocation, study participants will be individually requested by the members of the research team to complete the questionnaires. The flow diagram of the study design is depicted in Fig. 1.

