
### Objectives {7}

This study protocol describes a randomized controlled trial for patients with breast cancer and increased CRF receiving either Argentine tango in a tango group or no Argentine tango in a waiting-list control group. The primary outcome measure is the change of CRF levels after 6 weeks. (A) The CRF changes of patients of the tango group will be compared to the waiting-list control group, and (B) prior to and post the 6-week Argentine tango treatment, the CRF changes are evaluated for the whole study cohort. The primary hypothesis is that a module consisting of six consecutive weekly 1-h Argentine tango lessons will promote a significant reduction of fatigue symptoms. Secondary objectives are the improvement of self-reported sleep quality and HRQL, prior to and post the Argentine tango treatment, and to explore the effects after 6, 12, and 24 months follow-up.

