### Who will take informed consent? {26a}

It is the responsibility of the study physician to provide sufficient verbal and written information on the study’s purpose and procedures, information on data protection procedures, possible advantages and disadvantages of participation, and option to withdraw from the study at any time and without any given reason and to take informed consent. Written informed consent will be obtained from all participants prior to study enrollment.

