### Interventions

#### Explanation for the choice of comparators {6b}

The comparator is a waiting-list control group. All participants will be randomized to either the tango group or the waiting group. The participants of the waiting group will continue routine activities during the 6-week waiting period. During follow-up, patients from the waiting-list control group will receive the same Argentine tango module as the participants of the tango group. The follow-up assessments for both trial arms will be the same (Fig. 1).

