#### Intervention description {11a}

The Argentine tango program consists of six weekly 1-h tango sessions, which are conducted by a professional tango teacher and will be carried out in small groups of three to eight participants. Elements of movement and music of Argentine tango will be presented. The coordination, rhythm, and body awareness will be stimulated with harmonic movements to the tango music. Introductory exercises are practiced first without musical accompaniment and then with Argentine tango music. The 6-week program comprises breathing and relaxation exercises, balance finding, and includes tango walking and dancing elements as well as social interaction. The therapist will give explanations and lead guided exercises which are oriented towards walking to music, self-perceptions, and spatial perceptions as outlined in Table 1. Each group session will be structured in a warm-up, main part, and focused ending. The warm-up consists of a standing exercise with the feet open, with the imagination of moving through the body from the toes to the scalp and bringing awareness to the bodily sensations. The main parts have different focuses throughout the six sessions and include theoretical and practical instructions of walking and dancing techniques, repetitions with individual breaks, and explanations as needed (for details see Table 1). Each session ends with a 3-min standing exercise without movement, in silence with feet open and eyes closed.

**Table 1 Tab1:** Six-week Argentine tango protocol for people with breast cancer and fatigue

Session	Description of the activities
1	***Self-awareness*****.** Warming-up (standing exercise, open feet, imaging of moving through the body from toes to scalp bringing awareness to patient’s bodily sensations); axis and muscle tone; tension and relaxation; introduction of the tango position with feet closed, reaching in six directions (floor, sky, front, back, left, right); walking techniques, steps in four directions (forward, backward, left, right); walking forward in the line of dance with music; walking backward in the line of dance with music; changing directions in the line of dance from forward to backward while walking with music; and focused ending (standing exercise in silence with open feet and eyes closed, no movement)

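### The claim that waiting-list participants will not know they are waiting cannot hold for the 6-week self-reported comparison, and implies a protection against bias that the design lacks

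*Protocol article*

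**What the plan says.** All statements are in the protocol article.

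- **Who will be blinded {17a}** first concedes that "participants are not blinded to the tango treatment itself". The same sentence goes on to say that, since the control group is given the same lessons later, "they will not know whether they are in the waiting list or not". The section adds that the research team asks for questionnaires according to each participant's allocation.
- **Explanation for the choice of comparators {6b}** describes the control condition: "The participants of the waiting group will continue routine activities during the 6-week waiting period". It also gives the timing of their treatment: "During follow-up, patients from the waiting-list control group will receive the same Argentine tango module".
- **Intervention description {11a}** describes the experimental condition: "The Argentine tango program consists of six weekly 1-h tango sessions", led by a teacher in groups of three to eight.
- **Objectives {7}** sets the endpoint: "The primary outcome measure is the change of CRF levels after 6 weeks". Comparison (A) is tango against waiting list.
- **Who will take informed consent? {26a}** makes the study physician responsible to "provide sufficient verbal and written information on the study’s purpose and procedures".
- **Trial design {8}** and **Outcomes {12}** make fatigue, sleep quality and quality of life patient-reported.

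**The concern.** In this trial the participant is the assessor. The primary outcome and both secondary outcomes are her own ratings. If she knows she has had six weeks of a supervised group activity, or none, her ratings can reflect expectation, attention and the experience of going without, as well as any specific effect of tango.

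A waiting-list comparison is a legitimate design, and this mixture is its known price. The difficulty is that the blinding section, where a reader looks to judge that price, states that waiting status is hidden from participants. If that were true, part of the bias would be under control. If it is not, the section implies a protection that does not exist, and the 6-week difference would be read as more specific to tango than it can be.

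**Working it through.** No arithmetic decides this point. The check is who knows what between baseline and week 6.

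**1. What each arm experiences before the primary assessment**

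| | Tango arm | Waiting arm | Section |
|---|---|---|---|
| Weeks 0–6 | six weekly 1-h group sessions | usual activities, no tango | {11a}, {6b} |
| Week 6 | self-reports CFS-D, PSQI, QLQ-C30 | self-reports the same | {7}, {12} |
| After week 6 | follow-up | same module, then follow-up | {6b} |

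Controls are treated only after the 6-week assessment. At that assessment a participant has either been coming to tango each week or has not been at all. She cannot be unaware of which.

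**2. Does the stated reason support the claim?** The reason is that controls receive the same lessons later. That makes the arms alike in what they eventually receive. It does not make them alike during the six weeks that the primary outcome covers.

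**3. Does the rest of the article supply any concealment?** The article describes no sham, attention control or withholding of the existence of two groups. The informed-consent section points the other way, since purpose and procedures are explained verbally and in writing. The statement that participants, physicians and therapists are blinded to the randomization and allocation process concerns how assignments are made, not what a participant experiences afterwards. The teacher who leads the sessions also knows who attends.

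**4. Internal consistency.** The first half of the sentence says participants are not blinded to tango. In a comparison of tango with no tango, knowing whether one has had tango is knowing one's treatment status. The second half of the sentence takes back what the first half concedes.

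**5. Reach.** Affected at week 6 are the CFS-D total, the global PSQI and the 15 QLQ-C30 scales, so 1 + 1 + 15 = 17 scores, in all 60 planned participants. The sample size does not depend on the clause: {14} uses d = 0.8, 80% power and two-sided 5%, and none of these changes.

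**6. Baseline order.** The primary outcome is a change, so the baseline score enters it.
- Recruitment {15} and Plans for assessment {18a} place the questionnaires after consent and inclusion.
- Implementation {16c} mentions allocation first and then completion of questionnaires at dates that depend on course availability.
- {17a} says requests follow allocation.

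The article does not say when allocation is disclosed, so nothing shown fixes the baseline before disclosure, and nothing shown proves it comes after.

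**The case against.** The strongest reply separates two kinds of knowledge. A control may know that she has not yet had tango without knowing that she was randomized to wait. Groups are small, and Implementation {16c} links dates to availability for a course, so she might take the delay for ordinary scheduling. The article does not show the patient information or say how allocation is disclosed. This stands to a degree: the documents do not prove that participants are told their arm, and an argument resting on disappointment at having been randomized to wait would go too far. It does not rescue the clause, because bias in a self-rating needs only the knowledge of being untreated.

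Other stronger readings a reader might infer are not supported:

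- *That the text denies expectation effects.* No section mentions them, and the sentence openly says that participants are not blinded to tango. The protection is implied, not asserted.
- *That the report will credit the whole difference to tango.* The article already describes the contrast as tango against a waiting list, and no test, model or decision rule under Statistical methods uses the blinding clause. How the report will read cannot be known.
- *That the distortion can be given a size.* One could assume a bias of 0.1 to 0.3 SD and divide by the planned d of 0.8, giving 12.5% to 37.5%. The inputs are pure assumption. The result would apply to any unblinded waiting-list trial and so would measure the design, not the faulty sentence.

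**Conclusion.** The concern holds in this form: the clause on waiting status is wrong as written. It conflicts with the control condition, the intervention schedule, the 6-week endpoint and the first half of its own sentence. It implies a protection against expectation and reporting bias that the design lacks.

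The conclusion rests on two facts in the article: controls get no tango before the 6-week assessment, and the outcomes are self-reported. It needs no assumption about what participants are told of their arm. The documents give no size for the bias. Correcting the clause changes no sample size, test or estimate. It changes what comparison (A) may be said to show.

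It would be a mistake to read this as a fault in choosing a waiting-list control, or as evidence that baseline scores were in fact collected after disclosure.

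**What to change.** **Main change, for the whole trial.** In Who will be blinded {17a}, delete the clause on waiting status. State instead that participants and the therapist are unblinded and that the primary and secondary outcomes are self-assessed. State with comparison (A) that it estimates tango now versus waiting, including expectation and attention, and limit the conclusion to that. This costs a wording change and a more modest claim, with no added participants or staff.

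**Secondary step, for participants not yet enrolled.** Have the baseline CFS-D, PSQI and QLQ-C30 completed before allocation is disclosed, and write that order into Implementation {16c} and Plans for assessment {18a}. This keeps the baseline score free of knowledge of allocation. It does nothing for the week-6 score, where the main bias lies. Enrolment began on 10 June 2020 and is described as ongoing, so the step cannot reach those already enrolled and may make the baseline procedure differ between earlier and later participants. If it is adopted, the date of the change should be recorded.
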